#### Feasibility Measures

Study recruitment, adherence, and retention will be used to assess feasibility. Recruitment will be measured as the proportion of individuals enrolled compared to those who were approached and eligible but did not enroll. The proportion of weekly sessions attended by the participants will be calculated to assess adherence. Retention will be evaluated by the proportion of participants with complete data sets on primary outcome measures at pre and postintervention time points. Withdrawing will be calculated at the postintervention time point as the proportion of the participants who will withdraw from the intervention [72]. In addition, we will be collecting qualitative feedback and anecdotal information on how participants like the program, what they think about the program overall, and which component of the intervention was most or least enjoyed.

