### Procedure

#### Overview

The intervention program and assessments will be in person or remotely operated (on a university-licensed Zoom app), or a hybrid combination of in person and remote operation based on participants’ preference, their location, and context such as public health orders. After the research coordinator explains what is involved in the study, if a client is willing and eligible to participate, informed consent will be obtained. All participants will undergo 4 testing sessions: the first and second sessions will occur before enrollment in the intervention, and the third and fourth sessions will occur within 1 week and 3 months of the end of the intervention, respectively. In the first session (lasting approximately 2.5 hours), participants will complete a mental health screening battery. In the second, third, and fourth sessions (lasting approximately 1.5 hours), they will complete tests of resiliency, QoL, and neurocognition. If, as a result of the assessments, a clinically significant abnormal finding is obtained, the participant will be directed to seek medical advice from a health care provider. Various steps of the study and the roles of the study team are outlined in Figure 1.

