### Statistical Analysis

The objective of this project is to evaluate the efficacy of a CSN intervention for women who have experienced IPV-BI. This will be accomplished by quantitatively measuring resiliency, QoL, and neurocognition before and immediately after the intervention. A follow-up assessment will occur 3 months after the completion of the intervention to evaluate the maintenance of any gains in function. The mean (or median) for each assessment will be compared across testing times using 1-way ANOVAs. Relationships between BISA scores and the change scores for each assessment will be evaluated using regression analysis. Furthermore, the outcome of the intervention will be compared among various subgroups based on the findings of various mental health screening tools (eg, participants with PTSD vs participants without PTSD), substance use, and adverse childhood experience (eg, participants with adverse childhood experience vs participants without such experience). Various demographics and mental health screening assessments will be used to control for nonspecific effects of IPV. In addition, we will have opportunities to better characterize IPV-BI based on the BI load from the BISA tool, findings of various mental health screening tools, and cognitive findings using the Creyos assessment and task-switching paradigm. The α value will be set a priori at *P*<.05. All data will be analyzed using SPSS (IBM Corp).

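### Retention is measured only up to the post-intervention assessment, so women lost between that visit and the planned 3-month follow-up enter no feasibility measure

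*Protocol article*

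**What the plan says.** Feasibility is one of the two primary objectives (Objectives). Under Feasibility Measures the article names its components: "Study recruitment, adherence, and retention will be used to assess feasibility". Recruitment compares those enrolled with those approached and eligible who did not enroll. Adherence is the share of weekly sessions attended. Retention is fixed by visit and by data completeness: "Retention will be evaluated by the proportion of participants with complete data sets on primary outcome measures at pre and postintervention time points". A separate withdrawal measure follows: "Withdrawing will be calculated at the postintervention time point as the proportion of the participants who will withdraw from the intervention".

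The assessment schedule runs longer than the retention window. Under Procedure, Overview: "All participants will undergo 4 testing sessions", and "the third and fourth sessions will occur within 1 week and 3 months of the end of the intervention, respectively". The last session repeats the efficacy tests: "In the second, third, and fourth sessions (lasting approximately 1.5 hours), they will complete tests of resiliency, QoL, and neurocognition". Statistical Analysis gives its purpose: "A follow-up assessment will occur 3 months after the completion of the intervention to evaluate the maintenance of any gains in function". The Discussion expects the study to support later full-scale comparative and randomized studies.

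**The concern.** The outcome schedule has three time points after consent and screening: before the program, within a week of its end, and 3 months later. The retention rule uses the first two. A woman who completes the post-intervention tests and does not return at 3 months is counted as retained. She does not appear as a withdrawal either, because that measure concerns leaving the intervention. Recruitment and adherence cannot register her because both are settled by the end of the program. No feasibility measure in the article therefore covers the last 3 of the roughly 6 months from program start to final assessment (3 months of program plus 3 of follow-up).

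This matters because a later comparative trial with a follow-up visit needs to know whether survivors can be kept in the study after the scheduled sessions end. The measure as defined does not answer that question, and any difference between it and retention to study end can only run in the favourable direction. The efficacy analyses do not use the retention figure and are not affected.

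**Working it through.** **The plan's own figure.** There is none to reproduce. The article gives no expected retention, no expected dropout and no feasibility threshold. The sample size of 100 comes without an effect size, standard deviation or loss rate, so it does not help here.

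**Who is counted, by time of loss** (applying the rules as written):

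| Participant | Retained? | Withdrawn from the intervention? |
|---|---|---|
| Leaves the program before its end, no post data | No | Yes |
| Finishes the program, post data incomplete | No | No |
| Complete pre and post data, attends at 3 months | Yes | No |
| Complete pre and post data, lost before 3 months | Yes | No |

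The last two rows receive the same classification. The defect is confined to the last row.

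**Size.** Let r be the proportion of participants with complete primary-outcome data at pre and post (the article's retention). Let l be the proportion of those women without complete data at 3 months. I take all enrolled participants as the denominator. The documents give neither r nor l, so every value below is an assumption.

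- Retention as defined: r
- Retention by the same completeness rule through 3 months: r × (1 − l)
- Difference: r × l

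| r | l = 0 | l = 5% | l = 10% | l = 20% | l = 30% |
|---|---|---|---|---|---|
| 90% | 90% | 85.5% | 81% | 72% | 63% |
| 80% | 80% | 76% | 72% | 64% | 56% |
| 70% | 70% | 66.5% | 63% | 56% | 49% |

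Entries are retention through 3 months; the article's figure stays at r along each row. For l between 5% and 30% the difference runs from 0.70 × 0.05 = 3.5 to 0.90 × 0.30 = 27 percentage points. It is zero if nobody is lost after the post visit.

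**Worked case per 100 women,** r = 80% and l = 20%: 80 are complete at pre and post; 80 × 0.20 = 16 are lost afterwards; 80 − 16 = 64 are complete through follow-up. Of the 100 − 64 = 36 women lost or incomplete, 20 are correctly not counted as retained and 16 are counted as retained.

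**Direction.** Women complete at all three time points are a subset of those complete at pre and post, so the extended figure can never exceed the article's. This ordering holds under the same completeness rule. Simple attendance at a visit is a different measure, and the complete-data requirement can put retention below it.

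**The case against.** The strongest defence is that the retention window matches a stated purpose. The feasibility objective concerns the intervention, and the efficacy objective is met by comparing outcomes before and immediately after it, with the follow-up addressing maintenance only. Retention across that contrast is a coherent quantity, and the article names its time points openly. No retention threshold is stated, so no stated decision changes. All of this stands, and it is why the existing figure should be kept. It does not remove the gap: the objective lists retention under the study, the last outcome session falls 3 months after the window closes, and no other feasibility measure covers that interval. Nor is this a detail left to a fuller document, because the article itself fixes the rule and its visits.

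The documents do not support several stronger readings that a reader might infer:

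- *Everyone lost before the 3-month session counts as retained.* Women lost before the post visit, or with incomplete data there, are not retained.
- *The withdrawal measure also stops too early.* It is defined as withdrawal from the intervention, which cannot happen after the intervention has ended. Its timing is right.
- *The reported figure is bound to be inflated.* It exceeds retention to study end only if some women complete at the post visit are lost later, and no rate is given.
- *The number seen at 3 months will not be known.* Nothing suggests it will be withheld. Those outcomes are collected and compared across testing times, and numbers per visit are ordinary reporting that a condensed article may leave out.
- *Engagement simply ends with the program.* The navigator is to guide participants in keeping an activity log over the following 3 months. This does not guarantee attendance, but some involvement continues.

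**Conclusion.** The point holds in a limited form. The retention rule stops at the post-intervention visit although an outcome session 3 months later is planned and retention is part of a primary objective. Women complete at pre and post and lost afterwards count as retained, so the figure describes retention through the intervention and not through the study. Its excess over the latter equals r × l: 16 percentage points in the assumed case of 80% and 20%, and nothing if no such loss occurs. The direction follows from the definitions alone; the size rests wholly on assumed rates. The consequence falls on what the study can say about retention for later trials. I rate it a low-cost improvement to a badly fixed rule, and it does not threaten the efficacy results.

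**What to change.** In Feasibility Measures:

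1. Keep the pre/post figure and label it retention through the intervention.
2. Leave the intervention-withdrawal measure as it is.
3. Add, on the same stated denominator, the proportion with complete primary-outcome data through the 3-month session.
4. Report losses after the end of the program separately from losses during it.
5. Base the retention conclusion on both figures.

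This costs about one sentence. The 3-month session is already planned with the same tests, so no extra data collection is needed. The downside is a retention figure that may look less favourable.

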### Procedure

#### Overview

The intervention program and assessments will be in person or remotely operated (on a university-licensed Zoom app), or a hybrid combination of in person and remote operation based on participants’ preference, their location, and context such as public health orders. After the research coordinator explains what is involved in the study, if a client is willing and eligible to participate, informed consent will be obtained. All participants will undergo 4 testing sessions: the first and second sessions will occur before enrollment in the intervention, and the third and fourth sessions will occur within 1 week and 3 months of the end of the intervention, respectively. In the first session (lasting approximately 2.5 hours), participants will complete a mental health screening battery. In the second, third, and fourth sessions (lasting approximately 1.5 hours), they will complete tests of resiliency, QoL, and neurocognition. If, as a result of the assessments, a clinically significant abnormal finding is obtained, the participant will be directed to seek medical advice from a health care provider. Various steps of the study and the roles of the study team are outlined in Figure 1.

**Figure 1 figure1:**
[figure not shown]
Steps to participation, enrollment, and assessment with the program team. Right side of the figure provides various steps of the study, and the left side shows roles of the study team at various stages. CSN: community support network, PAR-Q: Physical Activity Readiness Questionnaire.

#### Structure of the CSN Intervention

The dose and sequence of the CSN rehabilitation intervention is outlined in Table 2.

**Table 2 table2:** An example of a 2 days per week schedule of the community support network rehabilitation intervention. The table provides the administration sequence and duration of aerobic exercise, cognitive training, and mindfulness meditation with an additional note on monthly peer group support discussion and biweekly counseling sessions.

Time	Duration^a^ (total duration/day: 2.5 hours)	Activities
9:30 to 10 AM	30 minutes	Aerobic exercise
10 to 10:10 AM	10 minutes	Break
10:10 to 10:50 AM	40 minutes	Cognitive training, block 1
10:50 to 11:10 AM	20 minutes	Mindfulness meditation
11:10 to 11:50 AM	40 minutes	Cognitive training, block 2
11:50 AM to noon	10 minutes	Wrap up

^a^Participants must commit to attending the program on a part-time basis for 3 months. The program is adaptable, with an example 2 days per week version outlined in this table.

The following activities will be provided to the participants in addition to the activities mentioned in Table 2:

There will be a peer group support group session for approximately 60 minutes once a month.The program includes counseling of approximately 60 minutes twice a week.There will be a participant navigator who provides trauma- and violence-informed advocacy and program or systems navigation support to participants and referrals to other community agencies or services as needed.

#### Program Team

All members of the program team will receive foundational training in IPV and trauma-informed practice. The CSN facilitators will take formal training on the BEARS program from ABI Wellness and will be certified for its administration. The research coordinator will receive formal training in the administration of the various assessment tools. The team will meet every other week, or more frequently as needed, to track the program and participant progress and address questions or issues that arise.

### Sample Size Estimation

To generate and design a study with adequate power, we estimated the required sample size based on previous data from our laboratory in both healthy participants and those with IPV-BI [34,35]. Power calculations are based on the desired end point to detect a change in each of the assessments across testing times. Therefore, assuming our published SDs for these measures and considering the potential for increased variability in this study population, a total sample size of 100 participants would provide a >90% probability that the study will detect a significant change score at a 2-sided 5% significance level.

### Statistical Analysis

The objective of this project is to evaluate the efficacy of a CSN intervention for women who have experienced IPV-BI. This will be accomplished by quantitatively measuring resiliency, QoL, and neurocognition before and immediately after the intervention. A follow-up assessment will occur 3 months after the completion of the intervention to evaluate the maintenance of any gains in function. The mean (or median) for each assessment will be compared across testing times using 1-way ANOVAs. Relationships between BISA scores and the change scores for each assessment will be evaluated using regression analysis. Furthermore, the outcome of the intervention will be compared among various subgroups based on the findings of various mental health screening tools (eg, participants with PTSD vs participants without PTSD), substance use, and adverse childhood experience (eg, participants with adverse childhood experience vs participants without such experience). Various demographics and mental health screening assessments will be used to control for nonspecific effects of IPV. In addition, we will have opportunities to better characterize IPV-BI based on the BI load from the BISA tool, findings of various mental health screening tools, and cognitive findings using the Creyos assessment and task-switching paradigm. The α value will be set a priori at *P*<.05. All data will be analyzed using SPSS (IBM Corp).

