**Methods:**

In this pre- and postexperimental design, women (aged 18 to 50 years) who are survivors of IPV and IPV-BI will be recruited from various community organizations serving survivors of IPV. Exclusion criteria will include current pregnancy and any diagnosed neurological disorder known to affect cerebrovascular, neurocognitive, or sensorimotor function. A CSN rehabilitation intervention that includes aerobic exercise, cognitive training, mindfulness meditation, and counseling will be administered. A trauma-informed approach will be integrated into the design and implementation of the program. Furthermore, the program will include a participant navigator who will provide trauma- and violence-informed advocacy and systems navigation support to participants, in addition to facilitating a monthly peer support group. The intervention will be provided for 2.5 hours a day and 2 days a week for 3 months. Participants will complete psychological assessments and provide clinic-demographic information in the first assessment. In the second (before intervention), third (after intervention), and fourth (at follow-up) sessions, they will complete tests of resiliency, QoL, and neurocognition. The estimated sample size is 100. The objective of this study will be accomplished by quantitatively measuring resiliency, QoL, and neurocognition before and immediately after the intervention. A follow-up assessment will occur 3 months after the completion of the intervention to evaluate the maintenance of any improvements in function. One-way ANOVAs will be used to evaluate the intervention outcome across the testing times. Relationships among various variables will be explored using regression analysis.

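### The 3-month visit is meant to evaluate whether gains are maintained, but the only across-time test named, an omnibus ANOVA, cannot tell a kept gain from a lost one

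*Protocol article*

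**What the plan says.** Resiliency, quality of life and neurocognition are measured three times: before the intervention (session 2), just after it (session 3) and 3 months later (session 4). On timing, Procedure, Overview says "the third and fourth sessions will occur within 1 week and 3 months of the end of the intervention, respectively".

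The Statistical Analysis section states what the last visit is for: "A follow-up assessment will occur 3 months after the completion of the intervention to evaluate the maintenance of any gains in function". The abstract's Methods paragraph says the same, that it is to "evaluate the maintenance of any improvements in function".

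The analysis named next is "The mean (or median) for each assessment will be compared across testing times using 1-way ANOVAs", with alpha set at .05. The abstract repeats it: "One-way ANOVAs will be used to evaluate the intervention outcome across the testing times".

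The section's other analyses address different questions. They are subgroup comparisons, adjustment for demographic and mental health measures, and this regression: "Relationships between BISA scores and the change scores for each assessment will be evaluated using regression analysis". The time points that define the change score are not given.

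Sample Size Estimation concerns detecting a "significant change score at a 2-sided 5% significance level" and says that "a total sample size of 100 participants would provide a >90% probability" of doing so.

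**The concern.** To evaluate maintenance, an analysis must separate a gain that is still present at 3 months from one that has gone. The null hypothesis of an ANOVA over three times is that all three means are equal. Any departure counts against it, including a rise followed by a full return to baseline. A significant result is therefore compatible with complete maintenance and with complete loss.

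This is separate from the question of whether a 1-way ANOVA respects the pairing of measurements within a woman. It remains after a change to a repeated-measures ANOVA.

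At stake is the only stated purpose of session 4. The across-time P value would not answer it. The natural fallback, testing session 4 against session 3 and taking a non-significant result as reassurance, would mostly reflect limited precision.

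**Working it through.** **Inputs from the protocol.** Three testing times; N = 100; two-sided 5%; power above 90% to detect a change. No effect size, SD, between-visit correlation or dropout rate is given, so the stated power cannot be reproduced directly.

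**Back-solved effect (assumption).** With a paired t test, 100 complete pairs and two-sided 5%, power is 90% when the mean gain divided by the SD of the paired difference is dz = 0.327. The normal approximation gives (1.960 + 1.282)/√100 = 0.324. The planned effect may be larger, since the text says more than 90%.

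**Between-time sum of squares.** Write the means as (baseline, post, follow-up).
- Gain fully kept, (0, d, d): mean 2d/3, so SS = 4d²/9 + d²/9 + d²/9 = 2d²/3.
- Gain fully lost, (0, d, 0): mean d/3, so SS = d²/9 + 4d²/9 + d²/9 = 2d²/3.
- Half lost, (0, d, d/2): mean d/2, so SS = d²/4 + 0 + d²/4 = d²/2.

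Kept and lost give the same SS.

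**Power of the omnibus test, repeated measures, equal correlations.** With unit SD and between-visit correlation ρ, the noncentrality is λ = n·SS/(1−ρ). Since dz² = d²/[2(1−ρ)], the kept and lost profiles both have λ = (4/3)·n·dz².
- n = 100: λ = (4/3)(100)(0.3273²) = 14.29. Power on 2 and 198 df is 92.9%, kept or lost.
- n = 80 (assumed attrition): λ = 11.43, power 86.0%, kept or lost.

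**Other forms of the test (n = 100).**
- Independent groups, as a literal 1-way ANOVA, d = 0.33 SD: λ = 100 × (2/3) × 0.33² = 7.26, power 66.8% for both profiles.
- Correlation that decays with time (first-order autoregressive, 0.7; d = 0.33; simulated): significant 97.5% of the time if kept and 99.6% if lost. The equality is now approximate, and the test favours the lost profile slightly.

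**Non-significance of session 4 versus session 3** (paired t, two-sided 5%, dz = 0.327, so a half loss is 0.164):

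| n | half the gain lost | all the gain lost |
|---|---|---|
| 100 | 63% | 10% |
| 80 | 70% | 18% |
| 60 | 76% | 30% |

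With a larger gain, dz = 0.5, a half loss is non-significant 30% of the time at n = 100 and 52% at n = 60.

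**Precision of session 4 minus session 3.** At n = 100 the 95% half-width is 1.984/√100 = 0.198 SDs of the difference, and 0.198/0.327 = 0.61. Even with an observed loss of zero, the interval would include a true loss of about 61% of the gain.

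**Does a named contrast do better?** Simulation at n = 100, dz = 0.327, ρ = 0.5, 20,000 runs:

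| True profile | session 4 − session 2 lower bound > 0 | and session 3 − session 2 lower bound > 0 |
|---|---|---|
| Kept | 89% | 83% |
| Half lost | 36% | 36% |
| All lost | 2.5% | 2.5% |

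The contrast separates kept from lost. The omnibus test does not.

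**The case against.** Several points on the other side have force.

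- **The aim is modest.** The text says evaluate, not demonstrate, and the Objectives section does not list maintenance as a primary or secondary objective. A reader might infer a formal non-inferiority aim and treat the absent margin as a defect. The documents do not support that: no such aim is stated, and margins and post-ANOVA contrasts are details an article may leave to an analysis plan not shown here. The point therefore rests on the test that is named not fitting the purpose that is named, rather than on what is left out.
- **No bad decision rule is written.** A reader might infer that the trial will report lost gains as maintained. Nothing says that a significant ANOVA, or a non-significant session 4 versus session 3 test, will be read that way. The miss rates above describe what would happen if that reading were adopted. Means reported at each time would also show the shape of the profile, although without a stated measure of its uncertainty.
- **The figures are not the plan's own.** The effect size, correlations and attrition are assumed, and miss rates fall as the effect grows. This affects the percentages but not the sum-of-squares identity, which holds for any d.
- **Comparing across times does not exclude pairwise comparisons.** True, but none is named for follow-up, and the change scores mentioned elsewhere are not tied to it.

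What stands is that the omnibus result, the only across-time analysis named, carries no information on whether a gain was kept or fully lost.

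**Conclusion.** The point holds as a mismatch between a stated purpose and the stated test. The omnibus ANOVA has equal power for a fully kept and a fully lost gain: exactly under equal between-visit correlations or independent groups, and approximately otherwise. Under the assumed dz of 0.327 with equal correlations, the repeated-measures form is significant about 93% of the time in both cases at n = 100. A follow-up minus baseline contrast would instead pass about 89% of the time if the gain is kept and 2.5% if it is lost.

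The consequence is confined to the follow-up aim. The pre-to-post efficacy comparison is not affected by this point.

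**What to change.** For the follow-up aim, replace reliance on the omnibus test with pre-set within-woman contrasts from a repeated-measures model for the three times:

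1. Session 3 minus session 2, with its 95% CI: the gain.
2. Session 4 minus session 2, with its 95% CI. Call a gain sustained only if a session 3 gain was shown and this lower bound is above 0.
3. Session 4 minus session 3, with its 95% CI, to show how much loss is compatible with the data.

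State that a non-significant session 4 versus session 3 difference will not be read as maintenance.

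A retained-fraction criterion is optional and the sponsor's choice. If used, set it before analysis and apply it only where a session 3 gain is shown. Otherwise it can mislead. For example, a rule that session 4 must exceed the average of sessions 2 and 3 is met by a profile (0, −d, 0), since 0 − (0 − d)/2 = d/2 > 0, although no gain occurred.

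**Cost.** A few sentences in the analysis section and three contrasts on data already planned. The Results section reports 6 women enrolled by October 2023, so at that date the text could be settled before most data existed. The downside is that a maintenance claim becomes somewhat harder to make: with the gain fully kept, the two-part rule for sustained passes about 83% of the time at n = 100 under the assumptions above.

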## Methods

### Design

This study will follow a pre- and postexperimental study design. Subsequently, a comparative study will be conducted by recruiting a control group receiving usual care.

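### The efficacy test is named as a 1-way ANOVA across testing times, without stating that time is a within-participant factor; read literally, it is conservative and does not match the change score behind N = 100

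*Protocol article*

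**What the plan says.** The Design section describes one group: "This study will follow a pre- and postexperimental study design". Under Procedure, Overview, "All participants will undergo 4 testing sessions", and the outcomes are collected at three of them: "In the second, third, and fourth sessions (lasting approximately 1.5 hours), they will complete tests of resiliency, QoL, and neurocognition". Each woman therefore contributes up to three values per outcome: before the intervention, within 1 week of its end, and 3 months after it.

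Only one test is named for the efficacy comparison. The Statistical Analysis section states "The mean (or median) for each assessment will be compared across testing times using 1-way ANOVAs", and the abstract states "One-way ANOVAs will be used to evaluate the intervention outcome across the testing times". Neither place mentions a repeated-measures, paired or mixed-model analysis for this comparison.

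The Sample Size Estimation section plans on a different quantity. It says "Power calculations are based on the desired end point to detect a change in each of the assessments across testing times". For N = 100 it claims power above 90%, and the event to which that power refers is that "the study will detect a significant change score at a 2-sided 5% significance level". It gives no effect size, SD or correlation between occasions.

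**The concern.** A 1-way ANOVA with time as the factor and no participant term treats the three sets of scores as if they came from three separate groups of women. Differences between women, which cancel when each woman is compared with herself, then stay in the error term. The standard error of a time difference is too large and the test is too cautious.

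A change score is a within-woman quantity, so the sample size is planned on one analysis and the efficacy question is answered by another. Efficacy is a primary objective, and this is the only test named for it. If the sentence is followed as written, a small true improvement could be missed although the study was large enough to detect it with a paired test. In addition, the sentence allows a comparison of medians, which an ANOVA does not make.

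**Working it through.** **Inputs from the protocol article.** N = 100, one group, three outcome occasions, 2-sided 5% level, power above 90% for a change score.

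**Inputs assumed, because none are given.** Equal SDs (set to 1), equal correlation r between any two occasions (0.3 to 0.8), complete data, and a mean pattern of (0, d, d), that is, a gain after the intervention that is fully kept at 3 months.

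**Step 1: the plan's own figure.** Power above 90% cannot be reproduced without an effect size and SD. It can be solved backwards for a paired change score. The smallest standardised change with 90% power is dz = (1.960 + 1.282)/√100 = 0.324, or 0.327 with the exact noncentral t. The claim is therefore attainable for a change of about 0.33 SD of the change score or more, provided the analysis is paired.

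**Step 2: standard error.** The variance of the difference between two occasion means is 2σ²(1 − r)/n. A 1-way ANOVA takes it to be 2σ²/n. The standard error is too large by 1/√(1 − r):
- r = 0.3: 1/√0.7 = 1.20
- r = 0.5: 1/√0.5 = 1.41
- r = 0.7: 1/√0.3 = 1.83
- r = 0.8: 1/√0.2 = 2.24

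**Step 3: type I error and power near the detection limit.** In units of the outcome SD, the effect with 90% paired power is d = 0.327 × √(2(1 − r)). The ordinary F(2, 297) test and the repeated-measures F(2, 198) test were simulated with 20,000 or more runs per setting. Separate runs differ by about one percentage point.

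| r | d (SD) | Type I error, 1-way | Power, 1-way | Power, repeated measures |
|---|---|---|---|---|
| 0.3 | 0.387 | about 1.5% | about 84% | about 93% |
| 0.5 | 0.327 | about 0.3% | about 67% | about 93% |
| 0.7 | 0.254 | near 0 | about 28% | about 93% |
| 0.8 | 0.207 | near 0 | about 7% | about 93% |

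The repeated-measures test keeps its 5% level. Its power is the same in every row because d shrinks as r rises: the noncentrality is n(2/3)d²/(1 − r) = 100 × (2/3) × 2 × 0.327² = 14.3 throughout.

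**Step 4: fixed effects.** Step 3 always places the effect at the paired test's detection limit. With d held constant over r = 0.3 to 0.8, the result looks different:
- d = 0.3 SD: 1-way power about 53% to 57%; repeated measures about 75% to above 99%
- d = 0.4 SD: 1-way power about 87% to 96%; repeated measures about 95% to above 99%
- d = 0.5 SD: 1-way power at least 98%; repeated measures above 99%

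The loss is serious for small changes and almost absent for moderate ones.

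**The case against.** **It may be shorthand.** One-way counts factors, and time is the only factor here, so the authors may mean a one-way repeated-measures ANOVA. Planning on a change score, and regressing change scores on BISA scores, suggest that they think of the data as linked within women. This stands as a real possibility: the text does not prove that the independent-groups test will be run. It does not remove the point, because neither place says so and a reader who follows the sentence runs the wrong test.

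**The error is on the safe side.** With positive correlation and complete data the literal test is conservative and would not create a false efficacy claim. That stands.

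**Power.** A reader might infer that most of the power is destroyed. The document does not support this, since it gives no correlation, SD or effect. The loss is modest at r = 0.3, about a quarter at r = 0.5 near the detection limit, and negligible for a 0.5 SD change.

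**Dropout.** A reader might also infer that selective dropout will bias the time means by some stated amount. Any such figure needs an invented dropout model, because the document gives no dropout rate, so none is claimed here.

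**Level of detail.** Contrasts after the overall F test and the handling of missing sessions can be left to an analysis plan. Their absence is not the defect; the defect is a method that is stated, twice, and does not fit the design.

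**Conclusion.** The point holds in a limited form. The test as worded does not fit three measurements on the same women, and it does not test the change score that justifies N = 100. Read literally, it overstates the standard error of a time difference by a factor of 1.2 to 2.2 for r between 0.3 and 0.8, and its true type I error lies well below 5%. Whether this matters for power depends on two quantities that the document does not give. For a change near the paired test's detection limit, power falls to between 84% (r = 0.3) and 7% (r = 0.8) instead of about 93%; for a change of 0.5 SD it stays at 98% or more. These figures assume equal SDs, equal correlations, complete data and a fully maintained gain. If the authors already intend a repeated-measures ANOVA, the standard-error and power problem disappears once they say so. The reference to medians would still need to go, and the contrast matching the powered change score should still be named.

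**What to change.** In the Statistical Analysis section and the abstract, replace the 1-way ANOVAs with a linear mixed model for repeated measures: time as a categorical fixed effect, a within-participant covariance structure, and all women with a pre-intervention assessment included. This also keeps women who miss a later session. The minimum alternative is a one-way repeated-measures ANOVA with a sphericity correction, which corrects the core fault but ordinarily uses only women with all three assessments.

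Name post minus pre as the primary contrast, which matches the powered change score, and the 3-month follow-up as the maintenance contrast. Delete the parenthetical reference to the median. If a different method is wanted for skewed scores, fix it in advance and not after seeing the data.

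The cost is a change of wording and slightly more analysis work. The data and the SPSS software already named stay the same.
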